## Abstract

**Background::**

Ischemic stroke is a major chronic noninfectious disease that seriously endangers health. Acupuncture is effective for ischemic stroke and less adverse reactions. However, there is not enough clinical trial data and solid evidence could confirm how acupuncture work to cerebral functional connectivity changes, and whether the changes is related to the different stimulation quantity.

**Design::**

This is a multicenter, central-randomized, controlled, double-blind, noninferiority, 2 factors and 3 levels orthogonal clinical trial. A total of 100 participants with ischemic stroke aged from 40 to 80 were randomized into experimental group and control group, the experimental group was divided into 9 groups (A1-A9) according to different factors or levels, and each group have 10 participants. The whole study period is 17 days, including 1 week for baseline observation, 3 days treatment and observation, and 1 week follow-up. Primary outcome is the fMRI based on blood oxygenation level dependent. Secondary outcomes included National Institute of Health Stroke Scale, Modified Barthel Index, Brunnstrom stroke recovery, stroke Chinese medicine symptom. Clinical assessments will be evaluated at before and the 0 hour, 24 hours, 36 hours after treatment, and 1 week follow-up. The primary outcome of the postacupuncture effect were investigated by paired T-test, and the continuous outcome variables will be analyzed with univariate repetitive measurement deviation analysis. Adverse events will be noted and recorded for the safety evaluation.

**Conclusion::**

The purpose of this study was to evaluate the central mechanism of acupuncture stimulation quantity using time and frequency as control conditions. This study will provide reasonable stimulation parameters and strong mechanism evidence of cerebral central network for the use of acupuncture for ischemic stroke.

**CHICTR registration number::**

ChiCTR1900023169. Registered 15 May 2019.

## Introduction

1

Ischemic stroke, also known as cerebral infarction, caused by blockage or narrowing in the arteries supplying blood and oxygen to the brain, is a common and frequently occurring diseases that threaten human health,^[1,2]^ which has characteristics included high morbidity, high disability rate, high mortality rate, high recurrence rate and high economic burden.^[3]^ With the acceleration of social aging and urbanization, the popularity of unhealthy lifestyles of residents, and risk factors of cerebrovascular diseases are extensive exposure, ischemic stroke has become a major cause of death, disability, and dementia worldwide.^[4]^

At present, thrombolytic therapy is the primary treatment for ischemic stroke. Although timely thrombolytic therapy can reduce the death and injury of nerve cells to some extent, the strict time window limit lead to the decrease of clinical utilization.^[5,6]^ In addition, there are still two thirds of patients with varying degrees of disability after successful intravenous thrombolysis,^[7]^ which makes it important to improve the recovery of neurological dysfunction after ischemic stroke.

Acupuncture as one of the oldest and most studied techniques in Chinese medicine as well known and used in some countries.^[8]^ Clinical studies have shown that acupuncture therapy could not only effectively promote neurological function recovery after ischemic stroke,^[9]^ improve poststroke symptoms,^[10]^ but also could enhance balance,^[11]^ reduce spasticity,^[12]^ and increase muscle strength.^[13]^

In China, more and more patients are willing to choose acupuncture for ischemic stroke because it can significantly improve the life quality. However, there is not enough clinical trial data and solid evidence could confirm how acupuncture work to cerebral functional connectivity changes, and whether the changes is related to the different stimulation quantity. Therefore, it is necessary to verify the effectiveness and mechanism of acupuncture stimulation quantity from senior quality studies. Functional magnetic resonance image (fMRI) has high temporal and spatial resolution, neuronal activity was measured by monitoring the hemodynamic response.^[14]^ It can objectively and visually evaluate different cerebral functional changes by acupuncture under physiological or pathological conditions.^[15]^ Now, the mechanism of the cerebral central network of differently acupuncture stimulation quantity treatment ischemic stroke is still unclear, and further rigorous clinical studies must be designed to confirm it.

This study's primary objectives are to evaluate the cerebral central network mechanism of differently acupuncture stimulation quantity treatment ischemic stroke based on fMRI, and its final conclusion will provide a high-quality clinical trial evidence for the crucial role of acupuncture stimulation quantity in the treatment of ischemic stroke.

## Methods and design

2

### Study design

2.1

This is a multicenter, central-randomized, controlled, double-blind, noninferiority, 2 factors and 3 levels orthogonal trial. A total of 100 participants were randomized into experimental group and control group, the experimental group was divided into 9 groups (A1-A9) according to different factors or levels, and each group have 10 participants. This trial recruited participants from 3 sub centers: the First Affiliated Hospital of Yunnan University of Traditional Chinese Medicine (TCM), the Affiliated Hospital of Yunnan University and Kunming Yan’an Hospital, recruitment advertisements will be placed on the network and bulletin boards. Eligible participants will have an equal chance of being allocated randomly to experimental group or control group.

The whole study period is 17 days, including 1 week for baseline observation, 3 days treatment and observation, and 1 week follow-up. Participants will be monitored cerebral functional connectivity changes by fMRI before and the 0 hour, 24 hours, 36 hours after treatment, and scales was used to evaluate the clinical efficacy during the treatment and follow-up period. Figure 1 shows a flowchart of the study.

**Figure 1 F1:**
[figure not shown]
Study design and participant flow chart.

### Study registration

2.2

This study protocol was registered on Chinese Clinical Trial Register (CHICTR), the register number is ChiCTR1900023169. It was performed in accordance with the Standard Protocol Items: Recommendations for Interventional Trials (SPIRIT).^[16]^ The clinical trial results will be reported according to the Standards for Reporting Interventions in Clinical Trials of Acupuncture (STRICTA).^[17]^

### Ethics

2.3

This study has been approved by the ethics committee of all sub centers. All the subjects involved will understand and sign the informed consent.

### Study time

2.4

The clinical study was originally scheduled to take place from January 2020 to October 2021. Recruitment has been delayed due to the COVID-19 outbreak and is expected to be completed in the first quarter of 2022 for all subjects.

### Study population

2.5

#### Inclusion criteria

2.5.1

The inclusion criteria contain the following items:

1.Subjects diagnosed with ischemic stroke in International Classification of Diseases (ICD-10-I63.902)^[18]^;2.Subjects diagnosed ischemic stroke for the first time, and the onset time is not more than 3 months;3.Subjects aged between 40 and 80 years old, male or female;4.Conscious, no dementia, normal communication and cooperation during examination;5.Right-handed.

#### Exclusion criteria

2.5.2

The exclusion criteria contain the following items:

1.Subjects diagnosed with hemorrhagic stroke in International Classification of Diseases (ICD-10-I61.902)^[18]^;2.Again stroke or onset time more than 3 months;3.Participation in any other clinical trial in recent 2 weeks;4.With aphasia and severe cognitive dysfunction;5.With severe heart disease, malignancy, kidney, and liver function insufficiency;6.Pregnant, lactating women, or contraindication history of magnetic resonance examination.

#### Dropout criteria

2.5.3

Participants who are unable to comply with this study, or who experience severe changes in their condition during treatment, will be dropped from the study.

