#### Experimental group

2.7.1

The acupoint prescription was “Shenyang Tongdu” acupuncture according to TCM theory and clinical experience. Acupoints are including DU14 (Dazhui), DU9 (Zhiyang) and DU4 (Mingmen). The experimental group adopted 2 factors and 3 levels orthogonal trial, the 2 factors of time and frequency include 3 levels of different parameters, and the intersection of different parameters constituted 9 groups (A1-A9). Time refers to the operating time, including 60 seconds, 120 seconds, 180 seconds. Frequency refers to the twists per minute without lifting, including 120 bpm, 180 bpm, 240 bpm, the range of twirling manipulations is about 180°. Participants only received acupuncture once, and the rest of the time was observation and follow-up period. Specific parameters of each experimental group are shown in Figure 2.

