#### Secondary outcomes

2.8.2

National Institute of Health Stroke Scale (NIHSS)^[20]^ scores for neurological deficit, Modified Barthel Index (MBI)^[21]^ scores for activities of daily living, Brunnstrom stroke recovery Scale^[22]^ scores for limb muscle strength, stroke Chinese medicine symptom Scale^[23]^ scores for curative effects of stroke. These scales will be used to evaluate efficacy at before and the 0 hour, 24 hours, 36 hours after treatment, and 1 week follow-up period. Participants’ diary for their temperature, breathe, heart rate, blood pressure, drugs, adverse events (AE), and others during the research was recorded. All the dropouts and causes will be documented in case report form (CRF). The study schedule is shown in Figure 3.

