### Adverse events

2.9

Any possible AE related to acupuncture intervention that occur, including nausea, subcutaneous bleeding or hematoma, needle stuck or breakage, and pain will be checked and treated. Details of AE will be recorded in the CRF by the acupuncturist and security administrator. Severe AE will be reported to the Ethics Committee. Participants who are unwilling to persist with the treatment will be removed from the trial.

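### The dropout and adverse-event rules remove participants from the trial, not only from treatment, so later assessments are lost selectively for those who do badly

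*Protocol article*

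**What the plan says.** Two sentences in the protocol article govern removal. Section 2.5.3 (Dropout criteria) provides that participants who cannot comply, or "who experience severe changes in their condition during treatment, will be dropped from the study". Section 2.9 (Adverse events): "Participants who are unwilling to persist with the treatment will be removed from the trial". In both, the participant leaves the study or trial as a whole, and neither mentions further assessment.

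Treatment is a single session. Section 2.7.1 says of the experimental arms: "Participants only received acupuncture once, and the rest of the time was observation and follow-up period". Section 2.7.2 says the same of the control arm. Section 2.8.2 schedules NIHSS, Modified Barthel Index, Brunnstrom and Chinese medicine symptom scores before treatment, at 0, 24 and 36 hours after it, and at 1 week. Section 2.8.1 schedules fMRI before treatment and at 0, 24 and 36 hours.

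The article also provides for recording. Section 2.8.2: "All the dropouts and causes will be documented in case report form (CRF". Section 2.9: "Details of AE will be recorded in the CRF by the acupuncturist and security administrator", and "Severe AE will be reported to the Ethics Committee". The abstract says that adverse events are recorded for the safety evaluation.

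**The concern.** The first rule depends on the outcome. A severe change in a stroke patient's condition is what the NIHSS and the other scales are there to measure, so removing the patient stops measurement just when it becomes informative. The second rule stands in the adverse-event section and can depend on tolerability. The trial compares nine combinations of manipulation time and frequency with each other and with a control prescription, and tolerability may differ between them.

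The session is given once. After it there is no treatment left to continue, so unwillingness to continue is no reason to end observation. An analysis plan can define analysis sets and methods for missing data, but it cannot recover visits that the protocol has stopped collecting. If removals differ between arms, the later comparison is between arms from which different numbers of poor results have been taken out.

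**Working it through.** The article gives no dropout rate and no figure that could be reproduced on this point. The check sets the rules beside the schedule and then shows how far one removal can move an arm.

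**1. Rules against schedule**
- Trigger: inability to comply or severe change (2.5.3); unwillingness to continue treatment (2.9).
- Consequence: exit from the study or trial.
- Assessments due after the single session: scales at 0, 24 and 36 hours and 1 week; fMRI at 0, 24 and 36 hours.
- Result: every assessment due after the removal is lost, and the loss is tied to how the participant is doing.

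**2. Arm size**
- Inputs from section 2.1: nine experimental groups and one control group, 10 participants each. 9 × 10 + 10 = 100, which matches the stated total and the 9:1 allocation in section 2.6.
- One removal is 1/10 = 10% of an arm.

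**3. Shift in an arm mean**
- Suppose k of 10 are removed and are on average W points worse than the mean of those kept. Then mean of all ten − mean of those kept = k × W / 10.
- k = 1: W = 2, 4, 8 gives 0.2, 0.4, 0.8 points.
- k = 2: W = 2, 4, 8 gives 0.4, 0.8, 1.6 points.
- Example: two of ten worsen by 4 NIHSS points and eight are unchanged. The mean change in all ten is (2 × 4 + 8 × 0)/10 = 0.8; in the eight kept it is 0.
- The values of k and W are assumed. A difference between two arms moves by the difference of their shifts, so equal losses of equal severity would cancel.

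**4. How often an arm would be touched**
- With an assumed removal rate d, independent between participants: P(at least one of 10) = 1 − (1 − d)^10, and P(at least two of 10) = 1 − (1 − d)^10 − 10 d (1 − d)^9.

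| Assumed d | At least one | At least two | Expected removals in 100 |
|---|---|---|---|
| 2% | 18% | 2% | 2 |
| 5% | 40% | 9% | 5 |
| 10% | 65% | 26% | 10 |
| 20% | 89% | 62% | 20 |

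**5. Safety**
- Before removal: adverse-event details and the cause of dropout go into the case report form.
- After removal: no further collection is stated. The recording sentence in section 2.9 follows one worded around events tied to the intervention ("Any possible AE related to acupuncture intervention that occur, including nausea, subcutaneous bleeding or hematoma, needle stuck or breakage, and pain"), so a deterioration judged unrelated may appear only as a cause of dropout.

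**The case against.** **Bad outcomes are not erased from safety.** A reader might infer that they disappear from the safety results. The documents do not support that: adverse events, dropouts and their causes are recorded, and severe events are reported to the Ethics Committee. Only events after removal are at risk of being missed. This part of the objection stands.

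**Earlier efficacy data are not said to be discarded.** A reader might also infer that removed participants vanish from the efficacy results altogether. No sentence says that data collected before removal are deleted or that only completers are analysed. Section 2.10 is silent, and analysis sets and the handling of missing data may properly stand in a fuller protocol or SAP that is not shown. This stands too. The point is therefore limited to data that would never be collected.

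**The window may be short.** The severe-change rule applies during treatment, and treatment is one session with 60 to 180 seconds of manipulation in the experimental arms. Read narrowly, worsening on a later day would not trigger it. But section 2.1 speaks of 3 days of treatment and observation, and the article does not settle which period is meant. Section 2.9 sets no time limit, and the non-compliance limb of section 2.5.3 is not clearly tied to treatment either. So the frequency is uncertain, but the defect in the wording remains.

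**The illustration uses a secondary outcome.** True. The primary outcome is fMRI, and keeping participants in follow-up may recover few scans in those who have become seriously unwell. The gain is mainly in the scales and in safety.

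**The adverse-event trigger is inferred.** The removal sentence in section 2.9 names no adverse event as its cause; the link rests on where the sentence stands. That is why tolerability is put here as a possible route only.

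**Conclusion.** The point holds in this form: the two rules make exit from the study or trial follow from severe change in condition, non-compliance or unwillingness to continue treatment, and do not separate this from stopping treatment. Later scale assessments would be lost selectively, and adverse events after removal may go unseen.

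Each removal is 10% of an arm and shifts that arm's mean by W/10 points. This can bias a comparison between arms when removals differ in number or severity. In a trial labelled noninferiority, losing the worst results from a poorer arm makes the arms look more alike. The actual bias cannot be stated, because it depends on a removal rate, on values of W and on a meaning of the treatment period that the article does not give. That a bias will occur, or that randomised comparability is already lost, does not follow from the text. The change should be made because the loss is avoidable and the visits are already planned.

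**What to change.** Leave all decisions on care and on stopping treatment to the existing clinical text. Change only the consequence for follow-up in sections 2.5.3 and 2.9, where participants are now *dropped* or *removed*. Suggested wording: *Stopping treatment does not end participation. Participants who cannot comply, whose condition changes severely or who do not continue treatment stay in follow-up. The scales and all adverse events are collected at the scheduled visits to 1 week unless the participant withdraws consent to follow-up. MRI is done where feasible. Data are kept in the allocated arm.*

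State also whether the treatment period in section 2.5.3 is the single session or the 3 days of section 2.1, so that it is clear when the rule applies.

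Cost: a short wording change and a few visits already in the schedule, in patients who are harder to assess. Some fMRI data will still be missing.

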### Randomization, allocation concealment, and blinding

2.6

After recruitment, a statistician who is not taking part in the clinical intervention will use SPSS 25.0 (IBM, Chicago, IL) to generate a random allocation sequence, the eligible participants who meet the inclusion criteria will be randomly distributed to experimental group and control group with proportion of 9:1. Participants in the experimental group will random reassignment to A1-A9 via the central randomization system by statistician from each sub centers. Each subject will received a unique random ID. The allocation concealment procedure will not be exposed until the clinical trial is finished completely. The baseline assessment and questionnaire administration was conducted by researcher A. Assessments and measurements of the participants will be carried out before and after the treatments by researcher B. Researcher C as image analyst will processed and analyzed the fMRI images to observed the cerebral functional connectivity changes. A licensed acupuncture researcher who has worked for more than 10 years will conduct acupuncture intervention on participants, whereas all subjects will deprived from knowing something about the pattern of treatment.

### Interventions

2.7

The intervention measures were selected according to the theory and experience of TCM. Both experimental group and control group received acupuncture treatment, but the prescription of acupoints was different. In addition, the use of conventional drugs in neurology department is allowed, such as antiplatelet drugs, antihypertensive drugs, lipid-regulating drugs, and drugs used will be documented in detail. This study used the same acupuncture instruments of disposable sterile needles (0.25 × 40 mm), acupoints location, and operation were carried out according to the National Standard of the People's Republic of China in 2006, Nomenclature and Location of Acupuncture Points (GB/T12346-2006).^[19]^

#### Experimental group

2.7.1

The acupoint prescription was “Shenyang Tongdu” acupuncture according to TCM theory and clinical experience. Acupoints are including DU14 (Dazhui), DU9 (Zhiyang) and DU4 (Mingmen). The experimental group adopted 2 factors and 3 levels orthogonal trial, the 2 factors of time and frequency include 3 levels of different parameters, and the intersection of different parameters constituted 9 groups (A1-A9). Time refers to the operating time, including 60 seconds, 120 seconds, 180 seconds. Frequency refers to the twists per minute without lifting, including 120 bpm, 180 bpm, 240 bpm, the range of twirling manipulations is about 180°. Participants only received acupuncture once, and the rest of the time was observation and follow-up period. Specific parameters of each experimental group are shown in Figure 2.

**Figure 2 F2:**
[figure not shown]
Treatment details for each experimental group.

#### Control group

2.7.2

The control group was treated with “Xingnao Kaiqiao” acupuncture, this is a standard prescription for stroke treatment in China, which has been proved effective in large sample trials. Acupoints are including DU26 (shuigou), and hemiplegia side PC6 (neiguan), HT1 (jiquan), LU5 (chize), BL40 (weizhong), and SP6 (sanyinjiao). The operation method is carried out according to the prescription, and the operation time is 2 minutes for each point. Participants only received acupuncture once, and the rest of the time was observation and follow-up period.

### Outcome measures

2.8

#### Primary outcomes

2.8.1

fMRI based on blood oxygenation level dependent (BOLD) is primary outcomes. The cerebral functional connectivity changes will be evaluate by magnetic resonance imaging at before and the 0 hour, 24 hours, and 36 hours after treatment. Siemens 3.0T MR scanner with 20-channel head coil was used. The MR scanning sequence included whole-brain 3D high-resolution T1WI and BOLD-fMRI. The changes of local cerebral functional activity were observed by the fractional amplitude of low frequency fluctuations (fALFF), regional homogeneity (ReHo), and degree centrality (DC). Seed point analysis was used to observe the changes of brain Functional connectivity (FC). If the brain regions and seed point show a high degree of time-domain consistency, it is considered that these brain regions together constitute a neural network related to some cerebral function. The more consistent the results of various analytical methods are, the higher the credibility of acupuncture in the brain effect area is.

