### Statistical analysis

2.10

The BOLD-fMRI data processing and analysis is based on the DPABI 4.3 of Matalab platform. Including removal of the first 10 time points, time correction, head movement correction (eliminating the data of head movement translation >2 mm or rotation shift >2°). Regression white matter and cerebrospinal fluid signals were used to remove interference. Spatial normalization, spatial smoothing, and linear drift removal were performed. If the data met normal distribution, the image characteristics of the postacupuncture effect were investigated by paired T-test.

Firstly, a gray matter mask was made for the subjects in this study, and the differences before acupuncture were found by paired T-test (*P* < .05). The whole brain gray matter mask was used to subtract the areas with significant differences before acupuncture, so as to exclude the pixels with significant differences at baseline. Paired T-test was used to investigate the changes of fALFF, ReHo, DC, and seed point FC before and after acupuncture in the intra-group comparison. Paired T-test was used to further find the differences in cerebral activity between groups compared with different stimulation quantity. The statistical results were corrected, if the threshold voxel level *P* < .01 and the cluster level *P* < .05, the difference was statistical significance.

Continuous outcome variables including NIHSS scores, MBI scores, Brunnstrom scores and stroke Chinese medicine symptom scores at before and the 0 hour, 24 hours, 36 hours after treatment, and 1 week follow-up will be analyzed with univariate repetitive measurement deviation analysis. Chi-Squared test will be used for comparison between groups.

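### The primary outcome is an imaging modality read as 12 unranked maps per arm, with no stated error control across maps, and agreement between metrics from one BOLD series is credited too highly

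*Protocol article*

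**What the plan says.** Section 2.8.1 of the protocol article defines the primary outcome in one sentence: "fMRI based on blood oxygenation level dependent (BOLD) is primary outcomes". The abstract likewise gives only the modality. Section 2.8.1 schedules "magnetic resonance imaging at before and the 0 hour, 24 hours, and 36 hours after treatment" and lists four derived measures: fALFF, ReHo, DC and seed-based FC. It ranks neither the measures nor the scans. Only one functional acquisition lies behind them: "The MR scanning sequence included whole-brain 3D high-resolution T1WI and BOLD-fMRI".

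The same section gives the only rule for reading the measures together: "The more consistent the results of various analytical methods are, the higher the credibility of acupuncture in the brain effect area is".

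Section 2.10 then tests all four: "Paired T-test was used to investigate the changes of fALFF, ReHo, DC, and seed point FC before and after acupuncture in the intra-group comparison". It goes on to between-group comparisons: "Paired T-test was used to further find the differences in cerebral activity between groups compared with different stimulation quantity". Significance is set at voxel level P < .01 and cluster level P < .05. No other correction is stated.

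**The concern.** A voxel and cluster threshold limits false findings inside one map. It does nothing about the number of maps examined. If every metric at every scan is primary, each arm or contrast offers 12 chances of a significant primary finding, and the article does not say which one decides or what follows if they disagree.

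The agreement sentence adds to this. It speaks of several analytical methods as though each brought separate support, yet all four are computed from the same time series in the same participants. Errors that reach one metric can reach another.

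This matters because the article expects firm conclusions from these maps. The abstract promises stimulation parameters and strong mechanistic evidence, and section 3 promises an optimal combination of time and frequency. With 10 participants per arm, different metrics or scans may favour different combinations, and nothing stated chooses between them.

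**Working it through.** **Inputs from the article.** Four metrics, three post-treatment scans and cluster-level .05 per map (sections 2.8.1 and 2.10). Nine experimental groups and one control group, 10 participants each (section 2.1).

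**The plan's own figure.** (9 + 1) × 10 = 100, which matches the stated total. The article gives no effect size, SD, power or margin, so nothing further can be reproduced.

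**Number of maps.** If each post-treatment scan is compared with the pre-treatment scan, 4 × 3 = 12 maps per arm. Over 10 arms, 12 × 10 = 120 within-arm maps. More than one seed would raise both counts.

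**Expected false maps under the null.** 120 × .05 = 6. This does not depend on correlation between maps.

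**Chance of at least one false map among 12.** If independent, 1 − 0.95^12 = 0.46. The metrics are unlikely to be independent and the article gives no correlations, so a range was simulated. Each map is represented by one z statistic, tested two-sided at .05, with 400,000 draws per setting. The correlations are assumptions.

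| Between-metric correlation | Between-scan correlation 0 | Between-scan correlation 0.5 |
|---|---|---|
| 0 | 0.46 | 0.42 |
| 0.5 | 0.40 | 0.36 |
| 0.7 | 0.34 | 0.30 |
| 0.9 | 0.26 | 0.22 |

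The most favourable setting, 0.22, is still more than four times 0.05.

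**What agreement is worth under the null.** Take one metric that is falsely significant at a scan. The probability that a second metric at that scan is also significant, in the same direction, is:

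- 0.025 if independent (half of .05)
- about 0.19 at correlation 0.5
- about 0.33 at correlation 0.7
- about 0.59 at correlation 0.9

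So a second agreeing metric is roughly 8 to 24 times as likely as independence would suggest (0.19/0.025 = 7.6; 0.59/0.025 = 23.6). The joint event stays uncommon: at correlation 0.9 it is .05 × 0.59 = 0.03 for a given pair. This is agreement at map level. Agreement on the same brain region was not modelled.

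**Would .05/12 per map be enough?** .05/12 = .0042 covers one arm or contrast only. Over 120 independent within-arm maps the chance of a false map would still be 1 − (1 − .0042)^120 = 0.39.

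**The case against.** **This is a condensed article, and the objective is mechanistic.** Seed choice, metric hierarchy and control across maps could sit in a full protocol or SAP, and several maps are not in themselves an error in mechanistic work. That holds for the detail. It does not cover a primary outcome section that itself names a modality and adds a rule for reading the metrics together.

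**A correction is stated.** It is, at voxel and cluster level. As described, it acts within a map.

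**The agreement sentence is only interpretive.** It speaks of credibility. It does not replace the significance threshold or make agreement a condition for a positive trial. Used as an extra screen, agreement can only narrow the set of regions believed. This stands, so the objection here is limited to the weight that the sentence gives to agreement.

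**A reader might infer that the four metrics will agree even without any effect.** The article does not support that. Under the null, two metrics cannot both be significant more often than one alone (5%). Section 2.10 also provides for head-motion correction and exclusion, white-matter and cerebrospinal fluid regression, and drift removal. How much shared nuisance remains is not known from the document, and it biases a paired test only if it shifts systematically between scans.

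**A reader might infer that the trial would be positive almost whatever the truth.** That needs any one of 120 or more maps to count as a positive primary result, and no section says so.

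**A reader might multiply the 12 maps by every pair of groups.** Section 2.10 does not say that every pair is compared at every scan, or that the control group takes part, so no between-group total is claimed here.

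**Conclusion.** The point holds in this limited form. The primary outcome is undefined below the level of the modality. Followed as written, the plan gives a chance of 0.22 to 0.46 of at least one false primary map per arm or contrast, against a nominal 0.05, and 6 expected false maps among the 120 within-arm maps if nothing changes.

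The agreement sentence overstates the evidence: agreement between metrics of one BOLD series is weaker than replication, by an amount that depends on their correlation.

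The 0.46 and the count of 6 follow from the stated metrics, scans, arms and threshold, given that each post-treatment scan is compared with baseline and that each map's error is exactly .05. The lower figures and the agreement probabilities rest on assumed correlations of 0.5 to 0.9. That the primary is unranked depends on no assumption.

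**What to change.** Before image analysis starts:

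1. Name one metric, at one post-treatment scan, in one prespecified network or seed, as the primary outcome.
2. Test it for the time effect and the frequency effect across the 90 experimental participants (9 × 10), with alpha shared over the two effects: .05/2 = .025 each.
3. Label all other metric-by-scan maps and all arm-level comparisons secondary or exploratory.
4. State that agreement between metrics is descriptive only.

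If all 12 metric-by-scan maps are to stay primary, the correction must cover the whole family. For the time and frequency effects that is 12 × 2 = 24 tests, so .05/24 = .0021 per map.

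The change needs protocol wording and no new data. The price is that fewer maps can be called confirmatory, and that the choice of metric, scan and network must be defended in advance.
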